# Implementing a lifestyle toolkit in individuals with cardiometabolic multimorbidity: study protocol for a cluster randomised, type III effectiveness–implementation trial (SHRADDHA-CMM)

**DOI:** 10.1186/s13063-026-09793-2

**Published:** 2026-06-02

**Keywords:** Cardiovascular disease, Cardiometabolic multimorbidity (CMM), ENDIRA, Cluster randomised controlled trial (c-RCT), SHRADDHA lifestyle toolkit

## Abstract

**Abstract:** Lifestyle modification, including dietary interventions, physical activity, and stress management, has proven crucial in the non-pharmacological management of cardiometabolic diseases. However, the implementation of these interventions in the context of cardiometabolic multimorbidity (CMM) within the unique demographic and cultural milieu of India is inadequately explored, despite Indians exhibiting distinct susceptibility to cardiovascular diseases. This community-based study aims to address existing knowledge gaps by implementing a culturally tailored lifestyle toolkit based on the WHO-HEARTS framework among individuals with CMM and exploring the intergenerational preventive dimension. The study adopts a two-arm non-blinded cluster randomised controlled trial (c-RCT) design to include adults diagnosed with CMM, defined by the presence of two or more of diabetes mellitus, hypertension, stroke, or coronary heart disease, aged 18 years and above, providing informed consent, and agreeing to follow-up. The trial spans the ‘Epidemiology of Non-communicable Diseases In Rural Areas’ (ENDIRA) cohort in Ernakulam, Kerala. The intervention, ‘SHRADDHA lifestyle toolkit’, integrates guidance on diet, physical activity, stress management, tobacco and alcohol cessation, and drug adherence. It leverages frontline health workers and a digital health platform for implementation. Measurements involve use of point-of-care devices and digital tools. The study duration is 24 months, with a sample size of 2000 participants distributed across 18 clusters. Statistical analysis includes repeated-measures ANOVA and multilevel models, employing an intention-to-treat approach. The study’s novelty lies in its holistic approach, addressing various facets of CMM comprehensively.

**Trial registration: **The trial has been registered with the Clinical Trial Registry of India (CTRI) Reference Number—CTRI/2025/08/092529. Registered on August 6, 2025

## Administrative information

Note: The numbers in curly brackets in this protocol refer to SPIRIT checklist item numbers along with spirit guidance. The order of the items has been modified to group similar items.

**Table Taba:** 

Title and structured summary	
Title stating the trial design, population, and interventions, with identification as a protocol {1a}	Implementing a lifestyle toolkit in individuals with cardiometabolic multimorbidity: protocol for a type III effectiveness–implementation trial (SHRADDHA-CMM)
Trial registration	
Name of trial registry, identifying number (with URL), and date of registration. If not yet registered, name of intended registry {2a}	Registered in Clinical Trials Registry—India: CTRI/2025/08/092529, dated 06/08/2025 https://ctri.nic.in/Clinicaltrials/rmaindet.php?trialid=99043&EncHid=16423.46502&modid=1&compid=19
Structured summary of trial design and methods, including items from the World Health Organization Trial Registration Data Set {2b}	Abstract contains background, design (two-arm non-blinded cluster RCT, type III implementation–effectiveness), setting (ENDIRA cohort, Ernakulam, Kerala), sample size (2000 across 18 clusters), intervention summary, outcomes, and main timepoints (baseline, 6, 12 months)
Protocol version	
Version date and identifier {3}	Version 4; date: 26 September 2025
Funding	
Sources of funding and other support (e.g. supply of drugs) {4}	This research study is supported by the Alliance for Health Policy and Systems Research
Roles and responsibilities	

Role of trial sponsor and funders in design, conduct, analysis, and reporting of trial; including any authority over these activities {5c}	Study sponsor does not have any role in the collection, management, analysis, and interpretation of data
Composition, roles, and responsibilities of the coordinating site, steering committee, endpoint adjudication committee, data management team, and other individuals or groups overseeing the trial, if applicable {5d}	Not applicable
Protocol and statistical analysis plan	
Where the trial protocol and statistical analysis plan can be accessed	Can be accessed in the CTRI website
Data sharing	
Where and how the individual deidentified participant data (including data dictionary), statistical code, and any other materials will be accessible {29}	Deidentified participant data will be shared on an individual request basis
Conflicts of interest	
Financial and other conflicts of interest for principal investigators and steering committee members {7b}	The authors declare that there are no competing interests
Dissemination policy	
Plans to communicate trial results to participants, healthcare professionals, the public, and other relevant groups (e.g. reporting in trial registry, plain language summary, publication) {31}	The results will be shared through peer-reviewed publication, the public and research community, and policy makers

## Introduction

### Background and rationale {6a}

Multimorbidity, defined as the coexistence of two or more chronic conditions in an individual, has emerged as a significant global health challenge, affecting nearly one-third of the global population [1, 2]. Its burden is particularly pronounced in low- and middle-income countries (LMICs), where rapid demographic and epidemiological transitions are driving rising prevalence [3]. In India, estimates of multimorbidity vary widely, ranging from 8.9 to 57% across studies [4]. Despite its ubiquity, research on multimorbidity in LMICs particularly in primary care and community settings remains limited and fragmented [5].

Cardiometabolic multimorbidity (CMM), a subset of multimorbidity, is especially important given its high prevalence, clinical complexity, and significant impact on mortality and disability [6]. CMM refers to the coexistence of two or more cardiometabolic conditions, including hypertension, diabetes, coronary heart disease (CHD), and stroke. Globally, cardiovascular diseases (CVDs)—the principal component of CMM—constitute a major health burden, with CHD and stroke ranking among the leading causes of mortality [7]. The situation in India is particularly concerning: CVD mortality rates (282 per 100,000) exceed the global average (233 per 100,000), accounting for more than one-quarter of total deaths and 14% of disability-adjusted life years (DALYs) lost [8].

Lifestyle modification—encompassing diet, physical activity, and stress management—has long been recognised as a cornerstone of non-pharmacological strategies for cardiometabolic risk reduction [9, 10]. Dietary interventions play a critical role in glycaemic control, with evidence demonstrating significant reductions in HbA1c through low-carbohydrate diets [11]. Similarly, the Dietary Approaches to Stop Hypertension (DASH) diet has consistently lowered blood pressure in diverse populations [12]. Nutritional interventions also support weight management by promoting energy balance, thereby reducing BMI and associated risks [13]. Beyond diet, cessation of tobacco and alcohol use exerts additional benefits; smoking cessation is associated with improvements in HbA1c and reductions in blood pressure [14, 15]. Stress management practices further contribute to better glycaemic control and lower blood pressure [16]. Physical activity is another key determinant, with robust evidence linking regular exercise to improved glycaemic control, lower blood pressure, and reduced cardiovascular risk. In addition, adherence to prescribed medications remains critical for secondary prevention among individuals with CHD or stroke and for maintaining blood pressure and glucose within recommended targets [17].

Although these interventions are well supported by global evidence, their effectiveness in the context of CMM, particularly within the diverse demographic, cultural, and health system contexts of India remains poorly studied [18]. Notably, Asian Indians exhibit increased susceptibility to cardiometabolic disease, often experiencing onset at younger ages compared to Western populations [19]. The burden is not uniform across India; for example, Kerala reports the highest prevalence of CVD of all Indian states [20]. Moreover, Indians frequently present with more severe manifestations, driven by genetic predispositions, environmental exposures, and lifestyle factors. This unique interplay underscores the need for tailored preventive and management strategies.

Several interventions worldwide have demonstrated the effectiveness of lifestyle modification in improving cardiovascular outcomes. The WHO-HEARTS technical package has been implemented in multiple LMICs, including India, showing feasibility in strengthening hypertension and CVD management through standardised protocols and primary care integration [21–23]. Similarly, trials in South Asia have shown that dietary counselling, tobacco cessation support, and promotion of physical activity can lead to improvements in blood pressure, glycaemic control, and body weight [24, 25].

Community health worker (CHW)–led interventions have been effective in bridging gaps in healthcare delivery, particularly for hypertension and diabetes control in underserved populations. For example, the HOPE-4 trial demonstrated that CHW-delivered lifestyle interventions, combined with simple drug regimens, reduced blood pressure and cardiovascular risk in LMICs [26]. In India, CHWs have successfully delivered structured counselling and follow-up for diabetes and hypertension management [27, 28].

Digital and mobile health (mHealth) platforms have further enhanced the delivery of lifestyle interventions, providing real-time feedback, reminders, and behaviour-change communication. Evidence from India and other LMICs shows that mHealth tools improve medication adherence, support tobacco cessation, and enhance dietary and physical activity practices [29–31].

Despite this promising evidence, important gaps remain. Most interventions have targeted single conditions such as hypertension or diabetes, rather than addressing the complex clustering of conditions characteristic of cardiometabolic multimorbidity (CMM). Few studies have evaluated integrated, multi-component toolkits combining diet, physical activity, stress management, substance cessation, and medication adherence in a unified approach tailored for CMM. While CHWs and mHealth platforms have been studied separately, evidence on their combined use for delivering structured, culturally tailored interventions in multimorbidity is limited. Importantly, the intergenerational dimension of cardiometabolic risk prevention has been largely overlooked, despite evidence of familial clustering of cardiovascular risk. Finally, very few interventions in India have explicitly adapted the WHO-HEARTS framework into a community-delivered lifestyle package that is regionally contextualised.

The Shraddha lifestyle toolkit is a culturally tailored adaptation of the WHO-HEARTS framework for South India. It integrates community health worker–led counselling with mHealth support to promote diet, physical activity, stress reduction, tobacco and alcohol cessation, and medication adherence. The toolkit will evaluate both clinical (HbA1c, blood pressure, BMI, adherence) and implementation outcomes (acceptability, adoption, cost). Uniquely, it also addresses the intergenerational dimension of cardiometabolic risk.

In addition, there is growing recognition of the intergenerational transmission of cardiometabolic risk. Evidence suggests that early-life exposures and parental health status can shape the cardiovascular health trajectories of offspring, highlighting the need for preventive strategies that extend beyond individual patients to families and future generations [32].

Against this background, our study seeks to address critical knowledge gaps by evaluating the effectiveness of a culturally tailored lifestyle intervention, adapted from the WHO-HEARTS framework, in improving outcomes among individuals with CMM in India [21]. Furthermore, by exploring the intergenerational dimension of CMM prevention, this study aims to generate insights that could inform innovative, family-centric strategies to mitigate the long-term burden of cardiometabolic disease.

We aim to bridge existing knowledge gaps by implementing a culturally tailored lifestyle toolkit based on the WHO-HEARTS framework in improving health outcomes among individuals with CMM in India [21]. We also aim to study the intergenerational preventive dimension of CMM, an aspect that has so far received limited attention.

### Objectives {7}

To identify the barriers and facilitators to implementing a lifestyle toolkit delivery model in individuals with cardiometabolic multimorbidity factoring for current lifestyle practices in managing cardiovascular disease (CVD).To co-develop and implement a context-specific lifestyle toolkit model tailored to the needs of the target population and support its iterative optimisation.To evaluate the optimised lifestyle toolkit model for acceptability, adoption, fidelity, coverage, and cost for implementation in a community setting.To evaluate the impact of the Shraddha lifestyle toolkit in improving glycaemia control (glycated haemoglobin), systolic and diastolic blood pressure, body mass index (BMI), and adherence to prescribed medications among individuals with cardiometabolic multimorbidity (CMM).

#### Research question

How can a co-developed, context-specific lifestyle toolkit achieve high coverage and equitable adoption of lifestyle practices for managing CVD among individuals with CMM in a community setting, using the WHO-HEARTS framework?

## Methodology

### Trial design {8}

Type III implementation–effectiveness using a two-arm non-blinded cluster randomised controlled trial (c-RCT) design.

### Trial setting {9}

The study is to be carried out in the ENDIRA cohort of Ernakulam, Kerala [22, 23]. The ENDIRA (‘Epidemiology of Non-communicable Diseases In Rural Areas’) cohort (*n* = 114,064) includes all individuals from five panchayats (villages) in Ernakulam district, Kerala. Four of the five panchayats have family health centres (FHCs), and one community health centre (CHC), which are further divided into 18 sub-centres and 75 wards having 2064 individuals with documented cardiovascular diseases. Among these individuals, 37.3% were diabetic, 53.5% hypertensive, 30.5% were dyslipidaemic, 16.8% were tobacco users, and 23.2% were alcohol users [24]. Leveraging previous research initiatives in this region ensures the seamless integration of the current study and enhances its generalisability to a broader context.

#### Rationale for selection

Leverages identified individuals with CMM from the ENDIRA cohort where there are high prevalence rates of cardiovascular diseases, aligning with the study’s focus on individuals diagnosed with diabetes, hypertension, stroke, or heart disease. Additionally, it builds on a WHO-Alliance–funded study which aimed at improving adherence to drugs for CVD in the same cohort.

### Sample size {14}

The sample size was determined using computer-generated randomisation at the cluster level across 18 sub-centres (9 intervention and 9 control).

As this is a type III implementation study, the primary focus will be on evaluating implementation outcomes. In addition, effectiveness will also be assessed based on the following sample size estimation.

To detect a minimum clinically meaningful difference of 0.5% in HbA1c between the two groups, with 80% power, a two-sided alpha of 0.05, and assuming a standard deviation of 1.5% [33], the required sample size under individual randomisation was calculated to be 142 participants per arm.

Given the cluster design, with a planned cluster size of 90 participants and an intracluster correlation coefficient (ICC) assumed to be 0.05, the design effect was calculated as 5.45 using the formula DE = 1 + (m − 1) × ICC. After adjusting for clustering, the required sample size was 774 participants per arm.

The trial will include nine clusters per arm, with 90 participants per cluster (810 participants per arm), which exceeds the minimum required sample size. The fixed cluster size and number of clusters are determined by the structure of the ENDIRA cohort, within which this follow-up study is embedded.

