### Strategies for achieving adequate participant enrolment to reach target sample size {15}

To achieve the target sample size, the study will leverage community health workers (ASHAs) to conduct household-based recruitment, ensuring inclusive enrolment of all eligible participants within each cluster from a community-benefit perspective.

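### The enrolment total is 2000 in two places and 1620 in the sample-size section, and on 16 degrees of freedom the unadjusted HbA1c comparison has about 77–78% power, not 80%

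*Protocol article*

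**What the plan says.** All references are to the protocol article.

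- **Abstract:** "with a sample size of 2000 participants distributed across 18 clusters".
- **Administrative information, item {2b}:** the same total, "sample size (2000 across 18 clusters".
- **Sample size {14}:** "The trial will include nine clusters per arm, with 90 participants per cluster (810 participants per arm), which exceeds the minimum required sample size". The calculation behind this is set up as "To detect a minimum clinically meaningful difference of 0.5% in HbA1c between the two groups", "with 80% power, a two-sided alpha of 0.05", "assuming a standard deviation of 1.5" percentage points. It assumes an ICC of 0.05 and a cluster size of 90, and arrives at 142 per arm before clustering, a design effect of 5.45, and 774 per arm after it. The section calls the cluster size fixed and attributes it to the structure of the cohort.
- **Strategies for achieving adequate participant enrolment {15}:** household recruitment is meant to reach everyone, "ensuring inclusive enrolment of all eligible participants within each cluster from a community-benefit perspective". The study implementation text under item {6b} likewise has every person identified with CMM in a cluster approached for consent.

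**The concern.** Two totals that differ by 380 participants cannot both describe this trial. They imply different cluster sizes and different design effects, so the printed 90, 5.45 and 774 belong only to the smaller one. A reader of the eventual CONSORT report would not know which figure to hold the trial to.

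The cluster size has a second problem. If all eligible people in 18 natural sub-centres are enrolled, the clusters will not each contain 90. The formula used for the design effect assumes equal sizes.

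Third, the statement that 810 per arm is more than enough for 80% power comes from a formula with normal quantiles. With only nine clusters per arm, the between-cluster variance is estimated from few units, and a test that respects this needs a larger critical value. At stake is the accuracy of the power claim for HbA1c, the only outcome for which the article gives a sample-size justification.

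**Working it through.** **Inputs (Sample size {14}):** difference 0.5; SD 1.5; two-sided alpha 0.05; power 80%; ICC 0.05; k = 9 clusters per arm; m = 90. For the larger total, m = 2000/18 = 111.1 (Abstract, item {2b}).

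**1. The plan's own figures**
- Individual randomisation: n = 2 × (1.960 + 0.842)² × 1.5² / 0.5² = 141.3, so 142 per arm. Reproduced.
- Design effect: 1 + (90 − 1) × 0.05 = 5.45. Reproduced.
- After clustering: 142 × 5.45 = 773.9, so 774 per arm. Reproduced.

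**2. The two totals**
- 18 × 90 = 1620, with design effect 5.45.
- 2000/18 = 111.1 per cluster, with design effect 1 + 110.1 × 0.05 = 6.51.
- Gap: 2000 − 1620 = 380. No attrition allowance or other step accounts for it.

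**3. Power with equal clusters**

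SE = 1.5 × √(2 × DE / (9m)), and the noncentrality is 0.5/SE. Degrees of freedom are 18 − 2 = 16, so the critical value is 2.120 instead of 1.960.

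| Total | m | DE | Effective n per arm | SE | Noncentrality | Power, normal | Power, t on 16 df |
|---|---|---|---|---|---|---|---|
| 1620 | 90 | 5.45 | 148.6 | 0.174 | 2.87 | 82.0% | 77.0% |
| 2000 | 111.1 | 6.51 | 153.7 | 0.171 | 2.92 | 83.2% | 78.3% |

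The difference detectable with 80% power on 16 df is 0.519 at 1620 and 0.511 at 2000. The ICC at which 80% would be reached is 0.0455 and 0.0476 respectively.

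**4. Unequal clusters**

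The article gives no coefficient of variation (CV) of cluster size, so a range is assumed. DE = 1 + ((1 + CV²)m − 1) × 0.05, with power from t on 16 df:

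| Assumed CV | DE, 1620 | Power, 1620 | DE, 2000 | Power, 2000 |
|---|---|---|---|---|
| 0.2 | 5.63 | 75.6% | 6.73 | 77.0% |
| 0.4 | 6.17 | 71.8% | 7.39 | 73.0% |
| 0.6 | 7.07 | 65.9% | 8.51 | 67.0% |

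**5. Baseline adjustment**

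The article gives no baseline–follow-up correlation r, so this is also assumed. If adjustment reduces total variance by the factor 1 − r² and leaves the ICC unchanged, the noncentrality is divided by √(1 − r²). With equal clusters:

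| Assumed r | Power, 1620 | Power, 2000 |
|---|---|---|
| 0.2 | 78.6% | 79.9% |
| 0.3 | 80.7% | 82.0% |
| 0.5 | 87.6% | 88.6% |

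**The case against.** The strongest defence concerns power. The plan's arithmetic contains no error: 142, 5.45 and 774 follow from the stated formula, and 810 does exceed 774. The shortfall on 16 df is 3.0 points at 1620 and 1.7 at 2000. Statistical analysis {20a} plans a multilevel repeated-measures model with individual covariates, and if baseline HbA1c is among them, a correlation of about 0.3 is enough to pass 80% with equal clusters. HbA1c is also not the main focus, because Sample size {14} puts implementation outcomes first. All of this stands. It makes the power part modest and conditional. It does not rescue the claim as printed, since the calculation is for an unadjusted comparison and invokes no baseline adjustment.

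The first-degree relatives mentioned under item {6b} do not explain the two totals: one per index participant would double 1620.

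A reader might infer several stronger points that the article does not support.

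- *That 2000 is out of reach because the trial setting describes* "18 sub-centres and 75 wards having 2064 individuals with documented cardiovascular diseases". The eligibility criteria accept any two of the four listed conditions, so a person with diabetes and hypertension but no cardiovascular disease qualifies. That list therefore does not bound the eligible pool.
- *That 90 per cluster cannot come from the cohort.* Dividing the same list by 18 counts people with cardiovascular disease, not people with CMM, so it shows nothing about 90.
- *That the total must be a recruitment stopping count.* The enrolment text reads as though recruitment ends when the eligible people have been approached. That is why the role of the number needs stating.
- *That the registry entry disagrees.* It is not available here, and nothing can be said about it.

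**Conclusion.** The concern holds in three parts of unequal weight. The contradiction between 2000 and 1620 is plain on the face of the article and needs no assumption. So is the conflict between a fixed 90 per cluster and enrolment of all eligible people. The power statement is right under its own normal approximation but overstated for 18 clusters: about 77% at 1620 and 78% at 2000, using the plan's difference, SD and ICC, equal clusters and an unadjusted comparison.

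Unequal clusters lower this, to about 76% down to 66% at 1620 and 77% down to 67% at 2000 for an assumed CV of 0.2 to 0.6. Baseline adjustment raises it by an amount that depends on an unstated correlation. It would therefore be too strong to say that the trial cannot reach 80%. What the documents support is that the stated calculation does not deliver it.

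**What to change.** 1. State one total in the abstract, item {2b} and Sample size {14}.
2. Say whether that total means 90 per sub-centre or everyone eligible. If it is 90, say how the 90 are chosen; if everyone, call the number an expectation and drop the word fixed.
3. Recompute the design effect for that total, using the cluster-size variation in the ENDIRA list.
4. Replace the claim that 810 per arm exceeds the requirement with power on 16 degrees of freedom.
5. If the multilevel model is to adjust for baseline HbA1c, say so, and give the assumed correlation, its source and the resulting power.

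The cost is a short recalculation and some wording. No extra participants are needed. The only downside is a slightly less favourable unadjusted power figure for an effectiveness outcome that is not the trial's primary focus.
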